**Expected outcomes:**

The results of this study will establish robust clinical evidence about the efficacy and safety of mXFP in the treatment of CU. A specific feature of this trial is that it is a integrative medicine trial with subjects being allowed to take the Western and Chinese medicine together for the treatment.

*Trial registration* This is registered on ClinicalTrials.gov, ID: NCT04967092. Register date: July 19, 2021. https://clinicaltrials.gov/ct2/show/NCT04967092.

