### Safety

No documented severe or serious event was reported using this herbal formula [23, 24]. However, there are still minor adverse events such as abdominal pain and dyspepsia. [25]. Safety will be assessed by laboratory parameters and participants’ reported adverse events and/or serious adverse events. All participants will be suggested to inform the study team about any adverse reaction during the treatment and follow-up periods. A direct telephone line will be provided so that subjects can report any adverse events during office hours between scheduled visits. Participants will be arranged to see our doctors if needed as unscheduled visits. All adverse reaction will be recorded, and the treatment suspended when any severe adverse reaction occurs.

Besides, in order to ensure participants’ safety, general data and routine blood test will be done before taking the medications. Blood test may induce bleeding, infection, bruising, and feeling lightheaded. When the needle pricks participant’s arm or hand, the participant may suffer a mild painful feeling, and the site maybe sore afterward. However, the risk of blood test is very low and discomfort is mild.

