### Sample size

The primary outcome is the UAS7 after 12 weeks of treatment. The minimal clinically important difference of UAS7 for measuring chronic urticaria ranges from 9.5 to 10.5 [26–28]. The standard deviation was estimated to be 12 from a previous study about the treatment of Chinese herbal formulae including Xiao-Feng Powder on Chinese patients with CU [24]. To detect a clinically meaningful difference of 10 in UAS7, with 80% power at the 0.05 significance level and an expected standard deviation of 12, 24 cases in each group are needed. To account for potential dropouts, a total of 58 subjects will be needed. PASS 12.0 was used for the sample size calculation.

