### Statistical analysis plan

All analyses will be conducted according to the intention-to-treat principle. Descriptive statistics will be computed for each of the analysed variables. The primary efficacy analysis will be done by comparing the two groups with respect to the UAS7 at baseline and at 6, 12 and 16 weeks after randomization using analysis of covariance (ANCOVA). Supplementary analyses will include a complete-case analysis and a linear mixed model analysis of all available data. Repeated measures ANCOVA will be used to test for group differences in the secondary outcomes, with adjustment for relevant baseline covariates. All statistical tests will be two-sided, and *p* < 0.05 is considered significant difference. The statistical software of SPSS 23.0 will be used for analysis.

Adverse events will be categorized, and the percentage of those experiencing mild and serious adverse events will be documented. Chi-square tests will be performed to examine differences in the proportion of total and categories of adverse events within each group.

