## Conclusion

In conclusion, this protocol will provide details for investigators about the mXFP in treating chronic urticaria. The results of this study would be able to contribute robust evidence concerning whether mXFP is effective and safe in the treatment of chronic urticaria. The results may also help to discover the underlying mechanism of this herbal remedy for chronic urticaria.

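### The planned chi-square tests at 24 to 29 patients per arm cannot support robust evidence on safety, above all for uncommon and serious adverse events

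*Protocol article*

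**What the plan says.** The Objectives section of the protocol article names efficacy and safety together as the single aim. The abstract, under Expected outcomes, states: "The results of this study will establish robust clinical evidence about the efficacy and safety of mXFP in the treatment of CU". The end of the Background makes a similar statement, and the Conclusion says the results should "contribute robust evidence concerning whether mXFP is effective and safe in the treatment of chronic urticaria".

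The Safety section lists the data: "Safety will be assessed by laboratory parameters and participants’ reported adverse events and/or serious adverse events". The Statistical analysis plan section gives the analysis. Descriptively, "the percentage of those experiencing mild and serious adverse events will be documented". Inferentially, "Chi-square tests will be performed to examine differences in the proportion of total and categories of adverse events"; read to its end, the sentence concerns "differences in the proportion of total and categories of adverse events within each group". The general rule is "All statistical tests will be two-sided, and *p* < 0.05 is considered significant difference".

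The Sample size section works only from a 10-point UAS7 difference with a standard deviation of 12, and concludes: "24 cases in each group are needed. To account for potential dropouts, a total of 58 subjects will be needed". It gives no expected adverse event rate and no power or precision for safety.

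**The concern.** Three stated elements do not fit together: a strong expectation about safety evidence, a sample size set on a continuous efficacy score, and a significance test as the only inference on adverse events. A test of no difference in a small trial can flag a large excess of harm. When it fails to reject, however, it says little about how large an excess remains possible. The p-value alone does not show that; an interval does.

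The wording adds a second difficulty. Read literally, a test inside each group does not compare mXFP with placebo at all. The calculations below take the reading more favourable to the plan, a between-arm test, and the limitation remains.

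At stake is the safety half of the objective for a herbal product added to bilastine for 12 weeks. A report of no significant difference could be taken as reassurance when the data still allow a substantial excess.

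**Working it through.** **Inputs from the article.** UAS7 difference 10, SD 12, power 80%, alpha 0.05 two-sided, 24 per group, 58 in total (Sample size); 1:1 allocation (Intervention), so 29 per arm randomised. 48/58 = 0.83, so the allowance for dropout is about 17%. The article gives no adverse event rate; every rate below is an assumption.

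**The plan's own figure.** For a two-sample t-test the noncentrality at 24 per arm is 10/(12 × √(2/24)) = 2.89, which gives power 0.807. At 23 per arm power is 0.789. The stated 24 per group is reproduced. The size is adequate for UAS7.

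**Results that need no assumed rate.** For a and b events in two arms of n, with m = a + b, the uncorrected Pearson statistic is X² = 2n[a(n−b) − b(n−a)]² / [n² m (2n−m)].

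- 3 against 0, n = 29: 58 × 87² / (841 × 3 × 55) = 3.16, p = 0.075.
- 3 against 0, n = 24: 48 × 72² / (576 × 3 × 45) = 3.20, p = 0.074.
- 4 against 0, n = 29: 58 × 116² / (841 × 4 × 54) = 4.30, above the 3.84 cut-off. When one arm has no events, at least four in the other are needed to reject.
- 6 against 3, n = 29: 58 × 87² / (841 × 9 × 49) = 1.18, p = 0.28. The observed excess is 3/29 = 10.3 percentage points; the Newcombe 95% interval is −9.0 to +29.3 points.
- No events in n patients: the one-sided 95% upper bound is 1 − 0.05^(1/n), which is 9.8% for n = 29 and 11.7% for n = 24. The two-sided 95% bound for n = 29 is 1 − 0.025^(1/29) = 11.9%.

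**Chance of missing a doubling, under assumed control rates.** Exact enumeration over two independent binomials, uncorrected chi-square, two-sided 0.05; the entries are 1 − power.

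| Control → mXFP | 29 per arm | 24 per arm |
|---|---|---|
| 5% → 10% | 90% | 92% |
| 10% → 20% | 81% | 83% |
| 20% → 40% | 62% | 67% |
| 30% → 60% | 36% | 41% |
| 40% → 80% | 11% | 16% |

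With Yates' correction the 10% → 20% row becomes 91% and 94%. At 29 per arm and a 10% control rate, 80% power needs about 41% on mXFP. Detecting 10% against 20% with 80% power would need 199 per arm.

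**Precision if the arms are truly equal.** The half-width of a simple 95% interval is 1.96 × √(2p(1−p)/n): 15.4 points at p = 10%, n = 29, and 22.6 points at p = 20%, n = 24.

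**The case against.** The strongest reply is that the harmful step is not in the document. A reader might infer that the trial promises to show mXFP is safe and will take p>0.05 as proof. The text does not go that far. The abstract speaks of evidence about safety, the Conclusion of whether the formula is safe, and nothing says how a non-significant test will be read. This stands, so the misreading is a risk and not a planned rule.

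A reader might also infer that the test would miss a doubling about 80% of the time in general, or that non-significance is nearly certain even if mXFP triples adverse events. Neither is supported. The 80% figure fits a control rate near 10%. Daily recording of side effects and assessment to week 16 could produce a much higher rate of total events, where a doubling is usually detected. Tripling from 15% to 45% is missed only 28% of the time at 29 per arm, and from 10% to 30% about 52%.

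Third, trials are ordinarily sized on the primary outcome, and interval methods are often left to a separate analysis plan, so their absence from an article is no fault. That is fair. The point here is different: the article does fix a method for safety, and sets beside it an expectation that the method cannot meet at this size.

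Finally, part of the safety reporting is already descriptive. That is also true, but percentages by arm without an interval for their difference do not show what excess remains possible.

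**Conclusion.** The point holds in a bounded form. The stated test and sample size do not support describing the safety evidence as robust. This is clearest for individual categories and serious events if they are uncommon: three against none is not significant at either sample size, and a zero count in 29 patients leaves rates of up to 9.8% open (one-sided 95%). These results rest only on the stated numbers of patients and the uncorrected chi-square.

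For total adverse events the size of the problem depends on a control rate the article does not give. Over assumed rates of 5% to 40%, the chance of missing a doubling runs from 90% down to 11% at 29 per arm, and from 92% down to 16% at 24. It is therefore serious if events are uncommon and modest if they are common.

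The sample size calculation for UAS7 is unaffected. The change is worth making because it concerns half of the stated objective and costs little.

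**What to change.** In the Statistical analysis plan section, replace the chi-square sentence. For total events, serious events and each category, report the proportion of patients with at least one event in each arm and the mXFP-minus-placebo difference with a 95% confidence interval (Newcombe or exact). Where an arm has no events, give the exact upper bound on the rate. State that a non-significant difference will not be taken as evidence of safety. The rewrite also removes the wording that places the test inside each group.

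In the abstract's Expected outcomes, at the end of the Background and in the Conclusion, keep the word robust for efficacy only and describe the safety data as preliminary.

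This needs no further patients, visits or data. The cost is a little more analysis and a less favourable statement about safety.

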### Objectives

The objective of the study is to evaluate the clinical efficacy and safety of mXFP on patients with CU.

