## Methods

### Study design

It is a multi-centred, randomized double-blinded placebo-controlled clinical trial with treatment duration of 12 weeks and post-treatment follow-up period of 4 weeks. We will randomly allocate the eligible subjects into two groups to receive either mXFP or placebo twice daily for 12 weeks followed by post treatment visits at week 16. Subjects will also take antihistamine standard therapy regularly for the first 6 weeks, and then for on-demand basis for the next 6 weeks during the treatment period.

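### The only adverse event test is written as a within-group test, so as worded it cannot compare mXFP with placebo

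*Protocol article*

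**What the plan says.** Two sentences at the end of the Statistical analysis plan section of the protocol article cover adverse events. The first is descriptive: "Adverse events will be categorized, and the percentage of those experiencing mild and serious adverse events will be documented". The second fixes the test: "Chi-square tests will be performed to examine differences in the proportion of total and categories of adverse events within each group".

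The contrast named there differs from the one used for efficacy in the same section: "The primary efficacy analysis will be done by comparing the two groups with respect to the UAS7". The secondary outcomes are likewise to be tested for group differences, but the Outcomes section does not list adverse events among them, so that sentence does not cover safety.

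The Objectives section reads: "The objective of the study is to evaluate the clinical efficacy and safety of mXFP on patients with CU". The Study design section describes the trial as follows: "It is a multi-centred, randomized double-blinded placebo-controlled clinical trial with treatment duration of 12 weeks and post-treatment follow-up period of 4 weeks". Under Intervention, both arms receive bilastine.

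**The concern.** A chi-square test within one arm can compare categories of event with each other, or participants with and without an event, or one visit with another. None of these uses data from the other arm, so none estimates or tests what mXFP adds.

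The control arm is there to supply that contrast. Because everyone takes bilastine, and urticaria patients on placebo also report events, the event rate in the mXFP arm alone cannot be attributed to mXFP. If the sentence were followed literally, the trial would report p-values for safety that do not address its safety objective. Such a p-value could be small when the arms are identical, and it carries no information when they differ.

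**Working it through.** **1. Contrasts as written, side by side**

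| Domain | Contrast in the article |
|---|---|
| UAS7 (primary) | between the two groups |
| Secondary outcomes | group differences |
| Adverse events | within each group |

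Adverse events are the only one of the three whose written test has no between-group contrast.

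**2. Number per arm**

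The Sample size section gives a difference of 10, SD 12, 80% power and a 0.05 significance level, taken here as two-sided in line with the Statistical analysis plan. The normal approximation is n = 2(1.96 + 0.8416)² × 12²/10² = 22.6, so 23 per group. With the t-test, power is 78.9% at 23 and 80.7% at 24, so the stated 24 per group is reproduced. The planned total of 58 at 1:1 allocation gives 29 per arm. The correction proposed here does not touch these figures.

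**3. What a literal within-group test does**

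The article gives no adverse event rates, so all counts below are assumptions. Take one literal reading: participants with an event against those without, tested against a 50:50 split, with expected count 29/2 = 14.5 in each cell.

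- 3/29: χ² = 2 × (3 − 14.5)²/14.5 = 18.24, p = 0.00002.
- 10/29: χ² = 2 × (10 − 14.5)²/14.5 = 2.79, p = 0.095.

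Now compare the arms.

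| mXFP v placebo | Within-group p (mXFP; placebo) | Between-group result |
|---|---|---|
| 3/29 v 3/29 | 0.00002; 0.00002 | p = 1.0 |
| 10/29 v 3/29 | 0.095; 0.00002 | χ² = 58(10×26 − 19×3)²/(29×29×13×45) = 4.86, p = 0.028; Fisher p = 0.056 |

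In the first row the arms are identical, yet both within-group tests are significant. In the second row the risk difference is 7/29 = 24 percentage points, yet the arm with fewer events is the one that reaches significance. Neither within-group result bears on mXFP against placebo.

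**4. What a between-group analysis can deliver at this size**

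Expected events per arm at an assumed 5% rate: 29 × 0.05 = 1.45, about 1.5. At 10%: 29 × 0.10 = 2.9. Both are below 5, the usual threshold for relying on chi-square, so individual categories call for an exact method.

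Approximate power at 29 per arm, two-sided 0.05:

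| Assumed placebo v mXFP rate | Power |
|---|---|
| 5% v 20% | 41% |
| 10% v 30% | 48% |
| 10% v 40% | 77% |

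For 80% power, the mXFP rate would have to be about 34%, 42%, 55% or 67% against placebo rates of 5%, 10%, 20% or 30%. The corrected test would therefore miss many real differences, which is why an estimate with an interval matters more than the p-value.

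**The case against.** The strongest reply is that the phrase is a slip. A difference in the proportion with any adverse event has no obvious second term inside one arm, and the surrounding sentences all compare groups. On that reading the authors intend a between-arm test and have used the wrong preposition. This is plausible, and it limits how serious the point is. It does not remove the point: the article has chosen a test and named its contrast, so this is not a detail left to a fuller document, and a reader who follows the text would run the wrong analysis.

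It can also be said that a between-arm significance test has little power here and that counts by arm carry most of the safety information in a trial of 58. That stands, and it is a reason to ask for a risk difference with an interval.

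A reader might go further in three ways that the article does not support:

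- **That a stated comparison with placebo has been dropped.** The objective names the safety of mXFP. The comparison with placebo follows from the design and is not spelled out.
- **That the safety comparison will never be made.** Events are collected in both arms, and percentages shown by arm would allow a descriptive comparison. What is missing is a specified between-group analysis.
- **That moderate or severe events will go unreported.** The plan to document "the percentage of those experiencing mild and serious adverse events will be documented" does mix a severity grade with seriousness, and the Safety section uses severe as a separate term ("the treatment suspended when any severe adverse reaction occurs"). But events are also to be categorised, totals and categories are to be tested, and the Safety section says that all adverse reactions are recorded. Grading scales and table layouts are commonly left to the full protocol, so this is only a note on terminology.

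**Conclusion.** The point holds in a limited form. The adverse event test is specified with the wrong contrast, and no other sentence in the article supplies the right one. As worded, it gives no information on whether mXFP adds adverse events over placebo, whatever the true difference. This follows from the wording alone; the p-values shown only illustrate it and rest on assumed counts.

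The weight is moderate. The primary outcome, sample size, randomisation and data collection are unaffected, and a wording slip is a plausible explanation. It should still be corrected before the data are unblinded, because safety is part of the objective.

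**What to change.** In the Statistical analysis plan section, change the contrast from within each group to between the mXFP and placebo groups. A suitable wording:

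*The number and percentage of participants with at least one adverse event, overall and by category, will be reported by arm and compared between the mXFP and placebo groups as a risk difference with 95% CI. A chi-square test will be used, or an exact test where expected counts are small.*

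The rule for switching to the exact test should be fixed in advance, since the two can fall on opposite sides of 0.05 (0.028 and 0.056 in the 10/29 v 3/29 example).

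As a minor addition, report severity and seriousness as separate classifications.

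The cost is wording only. Adverse events are already recorded in both arms, and the planned 58 participants do not change.

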### Data management and quality assurance

To protect patient privacy, all research data will be handled in line with Hospital Authority and Hospital’s policy in handling, storage and destruction of participants’ medical records. The data would be locked in cabinets where the department keeps the participants’ confidential information. Besides, all collected information will be input into a computer with restricted access to investigators only. Only de-identified data will be collected and removed from the premises. Participant information will be kept in storage for 7 years after the study and will be destroyed afterwards. 

### Ethical consideration and dissemination of information

This study will be conducted according to the Declaration of Helsinki and ICH-GCP. The ethical validity of the study was approved by the Joint The Chinese University of Hong Kong–New Territories East Cluster Clinical Research Ethics Review Committee (CREC Ref. No. 2021.085 T). Any modifications to the protocol will be reported to this committee, and amendment approval should be obtained before any changes can take place. Participants will be informed that the confidentiality of all information and data will be maintained anonymity. Consent forms should be signed by the participants before the study. All information will be encrypted and only the involved investigators can have access. Password is required to access the data. Participants are free to withdraw at any time without giving a reason or punishment.

## Discussion

Xiao-Feng Powder (XFP) is a widely used Chinese medicine formula for managing chronic urticaria (CU) in Chinese medicine and thus there is widespread interest in the potential role of modified Xiao-Feng Powder (mXFP) in the CU treatment. This prospective randomized double-blinded placebo-controlled clinical study allow evaluating the clinical efficacy and safety of mXFP in the treatment of CU in different aspects. It can help clarify the role of mXFP in future CU treatment. The study has several strengths: diverse advertisement and multi-centred recruitment enable enrolment of subjects from different groups, several clinically relevant follow-up visits enable the researchers to monitor the subjects’ body condition, double blind design minimizes subjective biases, and diverse study assessments enable comprehensive data analysis.

Frist of all, CU participants are recruited from three clinics which located on CUHK campus, and in Sha Tin and Wan Chai districts. Advertisements in the poster on the clinic and internet platforms, articles in local newspapers and magazines as well as health promotion talks will also be made to facilitate community recruitment. These enable more potential participants with CU who meet the eligibility criteria be recruited, and thus minimize the selection bias and ensure that the sample is representative of the CU population. Second, medical consultation will be arranged for each follow-up visit. Chinese medicine practitioners will assess participants’ body condition and participants are also required to record all medication intake and the side effects. These arrangements enable the researchers to monitor the body condition and the compliance of subjects during the treatment. Third, participants, clinicians and researchers are all blinded during the study. None of them would know if the participants were receiving mXFP or placebo until the study is completed. It can minimize the placebo effects, observer effect and bias. Fourth, efficacy of mXFP in different aspects can be evaluated by comprehensive study assessments. It can provide a full picture of information about the role of mXFP in CU treatment.

Nevertheless, a number of limitations require further comment. First, according to Chinese medicine theory, treatment is based on syndrome differentiation but not disease. mXFP is used to expel wind and eliminate dampness, clear heat, nourish the blood and stop itchiness, but not for deficiency of Qi and blood. Therefore, it is not suitable for all chronic urticaria subjects. Subjects are excluded if they have dual deficiency of Qi and blood. To enhance the reliability of inclusion, CMP will have detailed consultation with the subjects in screening. Moreover, Chinese medicine consultation will be held at every visit to keep monitoring the body condition. Second, as participants would intake both Western and Chinese medicine in the treatment, it may be difficult to show the causation between the efficacy of mXFP and urticaria treatment effect. However, the administration of oral mXFP and Bilastine adopts a dose regime similar to that currently used in daily practice. Although it may not directly reflect the causation, the correlation between the mXFP treatments and outcomes in real-world health system practice can be observed in the study. Moreover, the primary efficacy analysis will be done by comparing the two groups, the treatment and control group. Descriptive statistics will be computed for each of the analysed variables.

